### Recruitment strategies

Participants are being recruited from the general population through individual screening dates. Information channels are media alerts about two newspapers and a magazine for seniors, a regional senior club of retired people, and a health insurance company. The participants are being informed about the project and the planned study in a personal conversation (videoconferencing or phone call).

### Eligibility of participants

Individuals who are interested in the study contact the study centre. We offer them an appointment for screening, including a personal conversation about their screening results afterwards. People who fulfil the criteria for inclusion are informed about the study and asked to take part in the project.

Criteria for inclusion are (1) MCI, psychometrically operationalised by a score on the Montreal Cognitive Assessment (MoCA) ≤ 24 (cut-off for cognitive impairment) and at the same time a score on the Mini-Mental State Examination (MMSE) ≥ 24 (cut-off for no dementia); (2) possession of a computer, laptop, or tablet and basic skills in their use; (3) age ≥ 60; and (4) informed consent. Criteria for exclusion are (1) completely blind or deaf; (2) no personal computer, laptop or tablet; (3) normal cognition, operationalised by a score on the MoCA > 24; (4) dementia, operationalised by a score on the MMSE < 24; (5) acute depression, operationalised by a score on the 9-Item Patient Health Questionnaire (PHQ-9) ≥ 12; or (6) other psychiatric or neurological diseases (checklist): psychosis, (schizophrenia, major depression, mania, bipolar psychosis), Parkinson’s disease, multiple sclerosis, several strokes, alcohol abuse/drug abuse (addiction) and other serious brain diseases (especially brain tumour, brain injury, hydrocephalus). The drop out criteria are (1) withdrawal of consent, (2) serious illness or (3) death of the participant.

The MMSE and the MoCA are administered in combination in order to differentiate between normal cognition, MCI, and dementia. The MoCA is administered first in order to differentiate between normal cognition and MCI on the basis of the cut-off score of 24 points [24]. The MMSE is administered in order to differentiate between MCI and dementia on the basis of the cut-off score of 23 points [25]. For these cut-offs, we looked for an optimised ratio of sensitivity and specificity. The criteria for individuals who were positively screened for MCI, normal cognition, or dementia are shown in Table 2.

**Table 2 Tab2:** Definition of MCI

	Normal cognition	MCI	Dementia
**Step 1: MoCA**	30-25	24-0	24-0
**Step 2: MMSE***	-	30-24	23-0
**Decision**	**Exclusion**	**Inclusion**	**Exclusion**

*Abbreviations*: *MCI* Mild cognitive impairment, *MoCA* Montreal Cognitive Assessment, *MMSE* Mini-Mental State Examination. * MMSE was applied only if the MoCA results were in the range of 24 to 0 points

### Randomisation

Our external biostatistics partner is creating computer-generated randomisation lists (Institute of Medical Informatics, Biometry, and Epidemiology, Friedrich-Alexander University Erlangen-Nürnberg, [name]). All individuals meeting the inclusion criteria are randomised into one of the two groups (individualised CCT or basic CCT). Randomisation is software based and stratified by sex. Couples are assigned to the same group.

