## Methods and analyses

### Objectives

#### Research hypothesis

Individualised CCT (MAKSCog) will lead to statistically significantly greater improvements in cognitive capacities over time in people with MCI as compared with basic CCT (active control group).

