### Sample size and effect size estimation

A power analysis was computed with 100 study participants who were distributed to the two groups of the 2x2 factorial variance-analytic experimental design with one repeated measurement (factor 1: two CCTs; factor 2: two time points). With 50 study participants in each group, alpha = 0.05, beta = 0.20 (corresponding to a power of 80%), a correlation between repeated measures of 0.5 and a nonsphericity correction of 1, we will have the power to detect effects with an effect size of *f* ≥ 0.14 (comparable to Cohen’s *d* ≥ 0.28).

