### Data analysis

All relevant data, sociodemographic, health-related, primary, and secondary outcome variables will be reported descriptively. In order to be able to assess the quality of the randomisation, the baseline data from the intervention and control groups will be tested for statistically significant differences. For the multivariate analyses, we will impute missing values using the expectation maximum algorithm. The primary hypothesis will be tested by calculating multivariate analyses according to the general linear model. To ensure the robustness of the results, we will perform both analysis strategies ‘intention to treat’ and ‘per protocol’. ‘Intention to treat’ evaluations are carried out with all cases still alive at the end of the intervention or observation period. The significance level is defined as alpha = 0.05. The data analyses will be performed using the ‘IBM SPSS Statistics 24’ software. The members of the data monitoring committee are [name]. [name] and one of his statistics experts from the Institute of Medical Informatics, Biometry, and Epidemiology, Friedrich-Alexander Universität Erlangen-Nürnberg, [name].

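### Randomisation is stratified by sex but no sex term is stated for the analysis; adding sex and sex-by-time would be a small, nearly free gain in precision

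*Protocol article*

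**What the plan says.** Three places in the protocol article bear on this.

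- **Randomisation:** "Randomisation is software based and stratified by sex". The next sentence adds a second constraint: "Couples are assigned to the same group".
- **Sample size and effect size estimation:** the power analysis rests on a "2x2 factorial variance-analytic experimental design with one repeated measurement (factor 1: two CCTs; factor 2: two time points"). It assumes 50 participants per group, alpha 0.05, 80% power and "a correlation between repeated measures of 0.5 and a nonsphericity correction of 1", and arrives at a detectable effect of f = 0.14.
- **Data analysis:** "The primary hypothesis will be tested by calculating multivariate analyses according to the general linear model". The section also covers imputation, analysis sets, alpha and software. It lists no model terms, so sex is neither included nor excluded.

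The research hypothesis is about change. It expects "statistically significantly greater improvements in cognitive capacities over time in people with MCI as compared with basic CCT". Sex is among the baseline data listed in the questionnaire on sociodemographic and health-related data.

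**The concern.** Stratified allocation balances sex between the arms, so a sex difference in the analysed quantity contributes little or nothing to the true sampling variance of the arm contrast. A model without sex still counts that difference as residual error. Its standard error is then larger than the true one, the test is conservative, and the precision that stratification was meant to buy is not collected.

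The analysed quantity matters. With two time points, the group-by-time test compares mean change between arms. A sex difference that is the same at both times drops out of each person's change, so only a sex difference in change (sex-by-time) can widen the standard error. At stake is a small amount of precision for the primary MoCA comparison, and for any secondary cognitive outcome analysed by the same kind of model.

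**Working it through.** **1. Reproduce the plan's figure.** Inputs from the sample size section: N = 100, m = 2 time points, correlation ρ = 0.5, nonsphericity correction 1, alpha 0.05. For the group-by-time F test, λ = f²·N·m/(1 − ρ) = 0.14² × 100 × 2/0.5 = 7.84, with 1 and 98 degrees of freedom. Power is 0.792, and exactly 80% power needs f = 0.1415. The stated f = 0.14 therefore reproduces. A between-group test would need f = 0.245, so the trial was sized on group-by-time, without sex.

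**2. Effect of leaving out sex.** Let d be the sex difference in change, in within-sex SDs of change, and p the share of women. With arms balanced within sex, sex explains R² = p(1−p)d²/(1 + p(1−p)d²) of the variance of change. The unadjusted standard error is too wide by 1/√(1−R²) = √(1 + p(1−p)d²). The protocol gives neither d nor p. With p = 0.5 assumed:

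| d | R² | SE factor | Power at f = 0.14 without sex | with sex |
|---|---|---|---|---|
| 0 | 0 | 1.000 | 0.792 | 0.792 |
| 0.2 | 0.010 | √1.01 = 1.005 | 0.792 | 0.796 |
| 0.3 | 0.022 | √1.0225 = 1.011 | 0.792 | 0.800 |
| 0.5 | 0.059 | √1.0625 = 1.031 | 0.792 | 0.815 |
| 0.8 | 0.138 | √1.16 = 1.077 | 0.792 | 0.848 |

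The power columns hold the total SD of change at the planning value. With 60% women the factors are nearly the same (1.030 at d = 0.5). The row for d = 0.8 is an extreme, shown for scale only.

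**3. Check by simulation** (10,000 runs per setting, 25 per arm within each sex, no couples). The Monte Carlo error of a 5% rate is about √(0.05 × 0.95/10,000) = 0.2 points.

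- No sex effect: ratio of model SE to true SE 0.99, type I error 5.4%.
- Sex shifts MoCA level by 1 SD at both times, change unaffected: 0.99 and 5.4%, the same as with no sex effect.
- Sex shifts change by 0.3 SD: 1.00 and 5.0%. By 0.5 SD: 1.03 and 4.3%. By 0.8 SD: 1.07 and 3.3%.
- With sex in the model, the last two settings return to about 1.00 and 4.9%.

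**4. Why level effects cancel largely, not wholly.** The Eligibility section admits only MoCA scores of 24 or below, and the Data collection section uses the screening score as baseline. Baseline is therefore truncated and month 6 is not. Assuming normal scores, correlation 0.5 and a cut at the mean or 0.5 SD below it, a 0.5 SD sex difference in level leaves 0.17 to 0.20 SD in change. That makes the SE 0.4% to 0.5% too wide.

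**5. Couples act the other way.** With C couples sharing an arm and partner correlation r in change, the true variance of the contrast grows by about 1 + 2Cr/N. The protocol gives neither C nor r. Assuming r = 0.3 and d = 0.3:

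- C = 10: √1.06 = 1.030, so model SE/true SE ≈ 1.011/1.030 = 0.98 (simulated 0.97, type I error 5.4%).
- C = 20: √1.12 = 1.058, so 1.011/1.058 = 0.96 (simulated 0.95, type I error 6.1%).

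In these settings the unadjusted interval is too narrow overall.

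**The case against.** The strongest objection is that this argues from silence. The two-factor description belongs to a power calculation, and leaving covariates out of a power calculation does not fix the analysis model. The Data analysis section names a model class without terms, and covariates may be settled in an analysis plan that is not shown. This stands in part. A reader might infer that the stratum is definitely ignored, but the article supports only the statement that no sex term is given.

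A reader might also infer that intervals are too wide wherever sex is prognostic. For the group-by-time test that the trial was sized on, that is too broad, because a level difference largely cancels. A month-6 comparison, where level would count, is not described.

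A third tempting inference is that the error always runs towards wide intervals. That holds for the omission of sex taken alone. The rule that couples share an arm can reverse the net direction.

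Finally, the size is small and the planned power reproduces without sex, so no stated figure is wrong. This also stands. What remains is that allocation uses a factor for which the article states no role in the analysis, and that stating one costs almost nothing.

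**Conclusion.** The point holds as a minor improvement, not as an error in a stated figure. If the primary model contains only training and time, its standard error for the group-by-time contrast is about 0.5%, 1.1% or 3% too wide for assumed sex differences in change of 0.2, 0.3 or 0.5 SD. The corresponding loss of power is about 0.4, 0.9 and 2.4 points. Taken alone, the omission is conservative and cannot raise the false-positive rate. With no sex difference in change, nothing visible is gained or lost.

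These figures rest on assumed sex effects, a roughly even sex split and balanced allocation within sex. They say nothing about the net accuracy of the intervals once couples are counted, because the number of couples and the correlation between partners are not given.

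**What to change.** In the Data analysis section, state that the general linear model for the MoCA includes the stratification factor sex together with its sex-by-time term. The interaction is needed because a sex main effect alone does not enter the group-by-time test. If month-6 scores are analysed instead, enter sex as a covariate. Do the same for the MMSE and the computerised tests wherever a general linear model is used.

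The cost is one sentence, one added factor with its time interaction in the software model, and one error degree of freedom (98 to 97). No new data are needed, and the detectable effect of f = 0.14 can stay as stated. The sex term does not deal with couples; a separate sentence on how partners in the same arm are handled would settle that side.

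### Couples are allocated together, but the sample size and the primary model count every participant as independent, so the standard error is slightly too small if partners' MoCA change is positively correlated

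*Protocol article*

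**What the plan says.** Under Randomisation, the protocol article says that everyone who meets the inclusion criteria is randomised to one of two groups from computer-generated lists, and then: "Randomisation is software based and stratified by sex. Couples are assigned to the same group". It does not say how the couple rule works alongside the sex strata. Couples are not mentioned in any other section.

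Under Sample size and effect size estimation: "A power analysis was computed with 100 study participants who were distributed to the two groups". The only design factors named there are "factor 1: two CCTs; factor 2: two time points". The remaining inputs are "With 50 study participants in each group, alpha = 0.05", 80% power and "a correlation between repeated measures of 0.5 and a nonsphericity correction of 1". The result is a detectable effect of f ≥ 0.14.

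Under Data analysis: "The primary hypothesis will be tested by calculating multivariate analyses according to the general linear model". No couple term, random effect or robust standard error is named.

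**The concern.** The allocation rule and the analysis use different units. A man and a woman in a couple belong to different sex strata. Two independent draws would sometimes put them in different arms, so the rule can hold only if one draw decides for both. That makes the couple a randomised cluster of two.

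An ordinary general linear model and a power calculation on individuals assume that subjects are independent. Partners share a household and may share training habits over the six months. If this makes their changes in MoCA alike, two partners in one arm carry less information than two unrelated participants. The model would then understate the standard error of the group difference, give a p-value that is somewhat too small, and leave the stated power somewhat optimistic. The calculation has no reserve to absorb this, because it is set at exactly 80%.

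**Working it through.** **Step 1: reproduce the plan's figure.** Inputs from Sample size and effect size estimation: N = 100 (50 per group), m = 2 time points, correlation ρ = 0.5, nonsphericity correction 1, alpha 0.05. For the group-by-time interaction, the noncentrality is λ = f² · N · m / (1 − ρ), with 1 and 98 degrees of freedom.

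- At f = 0.14: λ = 0.0196 × 100 × 2 / 0.5 = 7.84, which gives power 0.792.
- Power of 0.80 needs f = 0.1415, which rounds to the stated 0.14.
- The between-subjects test would need f = 0.245, so the plan's figure is for the interaction.

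The stated figure therefore reproduces with 100 independent participants and no allowance for couples. With two time points, the interaction test is equivalent to comparing change scores between groups, so the correlation that matters is that of MoCA change, not of MoCA level.

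**Step 2: design effect for couples kept in one arm.** Let a share p of the n participants in an arm be in couples, with intra-couple correlation ICC for change and variance σ². There are np/2 pairs, and each adds 2 · ICC · σ² to the variance of the arm total. That variance is nσ² + (np/2) · 2 · ICC · σ² = nσ²(1 + p · ICC). Hence DEFF = 1 + p · ICC. The ordinary standard error is too small by a factor of √DEFF, and the effective N is 100/DEFF.

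**Step 3: consequences.** The type I error of the uncorrected test is 2 · P(t₉₈ > 1.984/√DEFF). The power of an analysis with the correct standard error uses λ/DEFF. The article gives neither p nor ICC, so all values of both below are assumptions.

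| p | ICC | DEFF | SE factor | Effective N | Type I error | Power at f = 0.14 | Detectable f |
|---|---|---|---|---|---|---|---|
| no couples | – | 1 | 1 | 100 | 0.050 | 0.792 | 0.1415 |
| 5% | 0.05 | 1.0025 | 1.001 | 99.8 | 0.0503 | 0.791 | 0.1416 |
| 10% | 0.2 | 1.02 | 1.010 | 98.0 | 0.0523 | 0.784 | 0.1429 |
| 20% | 0.3 | 1.06 | 1.030 | 94.3 | 0.0568 | 0.768 | 0.1457 |
| 40% (extreme) | 0.5 (extreme) | 1.20 | 1.095 | 83.3 | 0.0731 | 0.716 | 0.1550 |

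For example, at 20% and 0.3: DEFF = 1 + 0.2 × 0.3 = 1.06, √1.06 = 1.030, 100/1.06 = 94.3, and λ = 7.84/1.06 = 7.40.

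**The case against.** The strongest reply is that the effect is small and that the article is a condensed account.

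- **Size.** Both partners must separately be at least 60, score ≤ 24 on the MoCA and ≥ 24 on the MMSE, and stay below 12 on the PHQ-9. The Introduction gives an MCI prevalence of 6.7% at ages 60–64 and 25.2% at 80–84. If partners' status is roughly independent (an assumption), 40% in couples is above even the higher figure. Stable shared background, such as education, mostly drops out of a change score, and change also carries the measurement error of two tests, so an ICC of 0.5 is hard to defend. This stands, and it is why the lower rows of couple share and ICC should be read as the likely range.
- **Unseen analysis plan.** It could add a couple term. That is possible, and the missing detail alone would be no finding. But the article itself states the allocation rule, the power basis and the model family, and these do not fit together. A later analysis plan cannot change the power basis or clarify the allocation rule in retrospect.

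A reader might also infer more than the text supports:

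- *That partners are drawn from different lists.* The article gives no mechanism. One draw per couple, or a separate couple list, fits the text, and separate draws could not keep the same-group rule.
- *That one partner is not randomised.* A partner who follows the couple's draw is still randomised, as part of the couple. What is lost is independent allocation and possibly balance within that partner's sex stratum.
- *That leaving out sex makes the test conservative because sex predicts MoCA.* Data analysis lists no covariates either way; the two-factor layout belongs to the power calculation. Sex differences in level also cancel in the group-by-time test. Only a link between sex and change would matter.
- *That concealment is broken for a partner who joins later.* The article does not mention such participants. The student assistants who obtain consent do not know the allocation, and participants are not told their version. A later-joining partner might have seen the application at home, but this is a minor point.

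**Conclusion.** The point holds in a limited form. The couple rule makes couples the unit of allocation, while the stated sample size and primary model are built on independent individuals. The direction is anti-conservative only if MoCA change is positively correlated within couples.

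On the assumed 5–20% in couples and ICC of 0.05–0.3, the consequence is slight: a standard error too small by about 0.1–3%, type I error about 0.050–0.057, and a loss of at most 2.4 percentage points of power (0.792 − 0.768). A type I error of about 0.073 with an effective N of 83 needs both extremes at once and should not be quoted as the expected size. With very few couples the effect is negligible. The number of couples, which the trial will know, largely settles how much this matters.

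**What to change.** 1. **Randomisation:** state that a couple is allocated by one draw. For example, use a separate couple stratum and keep the sex strata for people who enrol singly. If recruitment is already complete, describe what was actually done.
2. **Primary model:** add a couple random intercept or couple-clustered standard errors, treating single participants as clusters of one, and include sex as the stratification factor. Apply this to the change score or to the 6-month MoCA adjusted for baseline. In a model of both time points, a couple intercept alone would capture similarity in level, not in change.
3. **Reporting:** give the number of couples per arm.
4. **Sensitivity analysis:** repeat the primary analysis with one partner per couple. If any partner enrolled after the couple's arm was fixed, note how many.

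The cost is one more model term, a mixed-model or robust-variance procedure in place of the plain general linear model, and a slightly wider interval. Items 2 to 4 need no new data beyond a couple identifier and remain possible after recruitment has closed.

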### Implementation

Participants do not know which treatment condition they are in, and the student assistants who assess the outcomes of the study are blinded to participants’ allocation.

For each intervention group, a set of download links was created and assigned to the participants in the according group. Similarly, any group-specific test material, e.g. the application-specific usability questionnaire at t6, is assigned by the study team in a sealed envelope.

### Interventions

Both computerised applications (intervention and control) are available for Windows PC/laptop and Android tablet and do not require a connection to the Internet. An Internet connection is needed only to install the application. The participants receive a download link for the respective application and the installation instructions one day before baseline testing. After baseline testing, the student assistants are available to help with the installation. If technical support is needed and the application cannot be installed at baseline, then the start date is set to the day of a successful installation.

	Layer sorting (‘Ebenen sortieren’)	A target picture of a vase with flowers is presented; the participant has to reproduce the picture out of layers; easiest: background–foreground, up to 5 layers with distractors	Visuoconstructional reasoning	Perceptual-motor
	Jigsaw puzzle (‘Bild zusammensetzen’)	Sorting of image sections	Visuoconstructional reasoning	Perceptual-motor
	Fill in the gaps (‘Felder füllen’)	A grid has to be filled in according to rules; each symbol is used only once in every row, column, and block; layout 4×4 to 9×9 fields	Working memory	Executive functions
	Remember cards (‘Karten merken’)	Remember a row of (up to 5) cards; compare new card to 5th to last card	Working memory	Executive functions
	Find pairs (‘Paare finden’)	Finding pairs of images in a pool; images covered; each turn two cards can be turned	Visuo-spatial memory	Perceptual-motor
	Spot the difference (‘Unterschied erkennen’)	A set of x identical pictures is presented, after a blank, the set and 1 extra pictures are presented; the extra picture has to be selected	Visual perception	Perceptual-motor
	Pattern recognition (‘Schema erkennen’)	A matrix of elements (combination of concentric geometrical figures) is presented; in one row or column, a figure is presented in the same position in all elements; the row/column has to be found; for small difficulties, hints are given	Decision-making	Executive functions
	Word conversion (‘Wörter umwandeln’)	Convert a source word to a target word in *x* steps; in each step, only 1 letter can be exchanged, and each line must contain a word	Word finding	Language
**basic CCT**	Rotating picture puzzle (‘Drehpuzzle’)	Picture is sectioned; sections are rotated; sections have to be turned in the right direction	Visuoconstructional reasoning	Perceptual-motor
	Picture quiz (‘Bilder quiz’)	Multiple-choice questions about images	Semantic and autobiographical long-term memory	Learning and memory
	Geography quiz (‘Länderspiel’)	Knowledge quiz based on German federal states	Semantic and autobiographical long-term memory	Learning and memory
	Dice game (‘Würfelpoker’)	Scoring points in a dice game by rolling five dice to make certain combinations (similar to Yahtzee), playing against a computer	Planning	Executive functions
	Shut the box (‘Klappbox’)	Roll two dice and count the number of dots on each die, sums or differences can be used; the aim is to get all numbers from 1 to 9 once; a player loses when a throw does not derive a new number	Planning	Executive functions

*Abbreviation*: *CCT* computerised cognitive training

